### Intervention

All participants will be asked to define a “quit date” (usually within a week of their baseline assessments or their first appointment at the smoking cessation clinic if in Group C, as per standard practice), on which they will be asked to stop smoking completely. This will be noted by the researcher and define follow-up visits.

Groups A and B will receive complimentary e-cigarette equipment and refills (Tornado V5, Joyetech, Shenzhen, China) at allocation stage, together with instructions on the correct usage of e-cigarettes. They will also receive behavioural support for a 3-month period. The nicotine strength of Group A cartridges will be up to 18 mg/ml nicotine strength, Group B will receive nicotine-free liquid.

Group C participants will be referred to NHS smoking cessation clinics and receive NRT in conjunction with behavioural support. Group C will be reimbursed for their prescription charges for the intervention period.

It is impossible for all study participants to receive behavioural support by the same person or at the same venue as e-cigarettes are not part of the local NHS strategy. To ensure that behavioural support is comparable between groups, all groups will receive the same level and type of behavioural support as currently offered as standard at NHS smoking cessation clinics [23], in the form of regular face-to-face or telephone appointments as per relevant guidelines (e.G. *minimum* of 6 support sessions within the 3-month period, offering practical advice and support, as detailed and structured in reference [23]). All advisors will have completed the same behavioural support training and will have previous NHS-based, SC experience. Behavioural support sessions for Group A and B will take place at easily-accessible locations with a choice offered to participants to match the service experience of Group C.

### Follow-up visits

*VISIT 2:* Within 3 days of “quit date”, vascular assessment of micro- and macro-vascular function *(see Outcomes).*

*VISIT 3:* 3 months past quit date, scheduled to coincide with current local NHS practice, all baseline measurements will be repeated, compliance will be measured in the resource use diaries as per NHS behavioural support strategy [23].

*VISIT 4:* 6 months past quit date, baseline measurements and compliance assessment will be repeated.

### Measures

*Baseline (Visit 1)*
Demographic data, including age and sex.Clinical history (including smoking history), previous operations, comorbidities, current medications, height, weight and blood pressure.Fägerstrom Test of Cigarette Dependence FTND; [24].EQ5D-5 L to support Health Economics’ assessment; [25].Q-Risk to assess risk of CVD; [26].Short Form (SF)- International Physical Activity Questionnaire (IPAQ) to assess physical activity; [27].Macro-vascular function [22],Upper-body micro-vascular function [28],“Finger prick” test to calculate the total cholesterol (TC) over High Density lipoprotein (HDL) ratio [29].Carbon monoxide (CO) breath levels [30].

### Outcome measures

The primary outcome will be macro-vascular function, a well-established independent predictor of long-term adverse cardiovascular events as determined by an FMD assessment [22], 6 months following participants’ “quit date”.

FMD is a non-invasive, nitric oxide-mediated measure, which independently predicts long-term adverse cardiovascular events [12] and has been used in numerous studies exploring smoking-induced physiological effects i.e. [12, 16]. Baseline scanning to assess resting vessel diameter will be recorded over 3 min, following a 10-min resting period. The brachial artery will be imaged at a location 3 to 7 cm above the antecubital crease to create a flow stimulus in the brachial artery. A sphygmomanometric cuff will be placed on the forearm; the cuff will be inflated at least 50 mmHg above systolic pressure to occlude artery inflow for 5 min. Recordings will commence 30s before cuff deflation and continuing for 3 min after. FMD will be expressed as a change in post-stimulus diameter evaluated as a percentage of the baseline diameter.

Secondary outcomes will include:Micro- and macro-vascular function at 3 days to define acute treatment effects and 3 months (interventions’ end).

Microvascular assessments using Laser Doppler Fluximetry and Iontophoresis as described in the literature; [28] will be performed at all study visits, in a temperature-controlled room (22–24 °C) in the ventral surface of the experimental (right) arm extended to the side at heart level. These will be used as indicators of the changes occurring in the endothelial –dependent and –independent vasodilatory function. Heart rate (Sports Tester, Polar, Finland) and blood pressure (left arm; Dinamap Dash 2500, GE Healthcare, USA) will be monitored at 5-min intervals throughout the protocol. The two drug delivery electrodes ((PF383; Perimed AB, Jarfalla, Sweden) will be positioned over healthy looking skin, approximately 4 cm apart with one containing 100 μL of 1% acetylcholine (ACh; Miochol-E, Novartis, Stein) and the other 100 μl of 1% sodium nitroprusside (SNP; Nitroprussiat, Rottapharm). A battery-powered iontophoresis controller (PeriIont PF382b; Perimed AB) will be used to provide the charge needed for ACh and SNP delivery. A 4 min stable recording of baseline flux will be followed by administration of the two agents according to the following protocol: 0.2 mA for 10 s (i.e., 2 mC), 0.2 mA for 15 s (i.e., 3 mC), 0.2 mA for 20 s (i.e., 4 mC), and 0.3 mA for 20 s (i.e., 6 mC), happening between 4-min intervals. To obtain an index of skin blood flow, cutaneous red cell flux will be measured by placing an iontophoresis laser-Doppler probe (PF481–1; Perimed AB), connected to a laser Doppler fluxmeter (PF5001; Perimed AB).b)Micro-vascular function at 6 months (measured as described for a).c)Smoking status at 3 and 6 months, self-reported and biochemically validated by exhaled air measurement of <10 ppm Carbon monoxide in line with the Russell Standard [30].d)change in CVD risk at 3 and 6 months compared with baseline, measured using Q-riske)Health Economic effects (assessed using EQ5D-L and a resource use diary) at 6 months. The EQ-5D is a generic measure of health status, where health is characterized on five dimensions (mobility, self-care, ability to undertake usual activities, pain, anxiety/depression).The EQ-5D has been validated in the UK and has been used in other clinical trials i.e. [31].f)Total cholesterol (TC) and High Density lipoprotein (HDL) via finger prick blood sample at 3 and 6 months; HDL is negatively affected by smoking [29], and improvements in the TC/ HDL ratio can be demonstrated 3 weeks after quitting [32].

### Qualitative exploration

We aim to explore the following topics:Factors that help smokers using e-cigarettes to quit smoking and deter smokers using e-cigarettes from quitting smoking, responding directly to a recent Public Health England call for more research on those areas [13].Experiences of treatment and advice given.Participant’s preference for trial allocation.Experiences of study participationParticipant acceptability of the intervention and study procedures.Methodological approach: Semi-structured in-depth interviews conducted either face to face or via telephone at 3-months post-group allocation with twelve to sixteen participants recruited using purposive sampling (mixture of genders, younger and older participants from all three intervention groups).

### Data analysis

SPSS 21.0 will be used to enter quantitative data and cleaning the data and to carry out missing values imputation and statistical analysis. Data will be reported and presented according to the revised CONSORT statement [33].

Analyses will be performed on an intention-to-treat basis. Double data entry will be implemented to to promote data quality. Where applicable, tests will be two-tailed with statistical significance being set at *p* ≤ 0.05. Baseline demographic (i.e. age, gender, HSI), physical measurements (e.g. weight, height, BMI), carbon monoxide and nicotine dependence levels, as well as Q-Risk, SF-IPAQ and EQ5D-L will be assessed for comparability between groups.

An Analysis of Variance (ANOVA) will be used to compare mean macro- and micro-vascular function between groups. A 95% confidence interval (CI) for the mean difference in these parameters between the three groups will also be calculated. In the event of differences between groups with respect to baseline measurements, multiple regression will be used to adjust the treatment effect for these variables, with the stratification covariates being included in the analysis. The ordinary least squares adjusted regression coefficient estimate for the e-cigarette groups’ parameter, along with its 95% CI, will then be reported. Secondary outcomes at 6-months will be analysed similarly. For repeated assessments at baseline, and at all follow-up sessions a summary measure (e.g. “Area under the Curve”) will be calculated for each participant.

Finally, a further subgroup analysis of those who ceased smoking completely will be undertaken and results will be compared amongst the three groups.

For qualitative data analysis, audio recording of the interviews will be made, transcribed verbatim, and the five stages of framework analysis of familiarisation, identifying a thematic framework, indexing, charting, and mapping will be followed [34, 35].

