Electronic (or “e-“) cigarettes or vaping devices uses battery power to disperse a solution that usually contains propylene glycol or glycerine, water, flavouring and nicotine [13]. They have become the most popular smoking cessation aid in England [14], while evidence suggests that they are efficacious as smoking cessation aids [15]. However, data on their effects on cardiovascular function is limited i.e. [16] and there is a lack of consensus within the smoking cessation community as to their potential impact: consequently, further research has been requested by the European Parliament [17], the British Medical Association [18], regulatory agencies, clinicians and researchers Lancet; [19], BMC Public Health; [20]. As e-cigarettes are not solely nicotine-based products, existing research exploring the effects of nicotine on the cardio-vasculature (e.g. coronary and peripheral vasoconstriction, intravascular inflammation and deregulation of cardiac autonomic function as well as inhibition of microcirculation; [21]) provides only limited information. Evidence is needed to inform the general public, smokers and policy-makers.

This study aims to assess effects on cardiovascular physiology in smokers making a quit attempt using e-cigarettes (either nicotine-free or nicotine-inclusive) in comparison with smokers making a quit attempt with prescription NRT.

The specific objectives of the study include:The comparison of the effects that nicotine-inclusive e-cigarettes (Group A), nicotine-free e-cigarettes (Group B) and NRT (Group C) have on cardiovascular physiology both acutely (e.g. within 3 days of “quit date”) and in the medium term (6 months following “quit date”), by measuring: a) endothelial-dependent, macro-vascular function and b) endothelial-dependent, micro-vascular function. The inclusion of Group B (nicotine-free e-cigarettes), will allow us to determine whether the e-cigarette vapour constituents have a distinguishable effect on cardio-vasculature against a nicotine-inclusive e-cigarette (Group A).Comparison of the effect of the different treatments on cardiovascular disease risk.An in-depth exploration of the participants’ study experience in a sub-sample of participants.Defining facilitators and barriers of smoking cessation in each of the 3 groups.Assessing the economic cost implications that the approaches have on the NHS and the study participants, by undertaking a Health Economics’ Cost Utility Analysis.

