## Methods

### Design

A pragmatic, 3-group, randomised, assessor-blinded, single-centre trial exploring the cardiovascular physiological effects of the use of e-cigarettes (nicotine-free and nicotine-inclusive, assessed separately) combined with behavioural support as a smoking cessation method in comparison to the combination of NRT and behavioural support.

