### Sample size

For the purposes of sample size estimation the primary outcome will be macro-vascular function, at 6-months post-“quit date” follow-up, as measured by % Flow-mediated dilatation FMD; [22]. For our calculations we used commercial software (G*Power 3.1.7, HHU of Düsseldorf).

Based on the primary outcome and using data comparing the short-term effects of e-cigarettes on macro-vascular function (measured by %FMD) in smokers and non-smokers (S.D. in the smokers’ group prior to e-cigarettes’ use = 3.23%, expected brachial FMD% difference between NRT group and e-cigarette users = 1.89%; 16). Using G*Power 3.1.7 (HHU of Düsseldorf) we calculated that we will need 66 participants in each group to detect a difference in macro-vascular function at 6 months (significance level = 0.05; power = 80%). Accounting for an estimated 25–30% dropout rate in-line with other e-cigarette-based RCTs [15], we aim to recruit 86 participants in each group (258 in total).

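### The adjusted regression reports one coefficient for both e-cigarette arms, so it gives no adjusted nicotine versus nicotine-free comparison

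*Protocol article*

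**What the plan says.** The Design section of the protocol article describes a three-group trial with the e-cigarette arms "nicotine-free and nicotine-inclusive, assessed separately"; the abstract says the same. Among the objectives in the Background, the reason given for having Group B is that it "will allow us to determine whether the e-cigarette vapour constituents have a distinguishable effect on cardio-vasculature against a nicotine-inclusive e-cigarette (Group A". A versus B is therefore a stated question of the trial.

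The Data analysis section has two steps. The first is an ANOVA of macro- and micro-vascular function across the groups, with this addition: "A 95% confidence interval (CI) for the mean difference in these parameters between the three groups will also be calculated". The second is conditional. If the groups differ on baseline measurements, a multiple regression that includes the stratification covariates adjusts the treatment effect, and then: "The ordinary least squares adjusted regression coefficient estimate for the e-cigarette groups’ parameter, along with its 95% CI, will then be reported". Secondary outcomes at 6 months are to be handled in the same way.

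The Sample size section rests on one contrast: "expected brachial FMD% difference between NRT group and e-cigarette users = 1.89" percentage points, with "S.D. in the smokers’ group prior to e-cigarettes’ use = 3.23". It gives no expected difference between A and B.

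**The concern.** In the regression sentence the estimate, the parameter and the interval are all singular, while the e-cigarette groups are plural. The natural reading is one indicator for e-cigarette against NRT. Such a model treats A and B as the same treatment. It cannot return A-C or B-C separately, and it contains no A-B contrast.

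The adjusted result matters most when the groups turn out unbalanced at baseline, because that is when the unadjusted means are least trusted. As written, that is also when the adjusted answer on nicotine against vapour is missing. If A and B act differently, the reported number averages them. If they act in opposite directions, it can be near zero while both arms differ from NRT.

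**Working it through.** **1. What the model needs.** With C as reference, a three-arm factor has two indicators: FMD = b0 + bA·(in A) + bB·(in B) + covariates. Then A-C = bA, B-C = bB and A-B = bA − bB. A single parameter g replaces this by FMD = b0 + g·(in A or B) + covariates, which forces bA = bB and so fixes A-B at zero by construction.

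**2. What the single coefficient estimates.** Leaving covariates aside, g = [nA·(A−C) + nB·(B−C)] / (nA + nB). With equal arms this is the plain average of the two effects.

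**3. Numbers.** The plan gives no value for this point, so the arm effects below are assumptions; only the 1.89 comes from the Sample size section.

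| Assumed A-C | Assumed B-C | True A-B | Single coefficient |
|---|---|---|---|
| 1.89 | 1.89 | 0 | (1.89 + 1.89)/2 = 1.89 |
| 1.89 | 0 | 1.89 | (1.89 + 0)/2 = 0.945 |
| 0.945 | −0.945 | 1.89 | (0.945 − 0.945)/2 = 0 |

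The coefficient is right for both arms only in the first row, where A and B do not differ. A simulation of the second row (66 per arm, SD 3.23, 4,000 trials) gave a mean coefficient of 0.946.

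**4. How often the regression might be used.** The Data analysis section lists 11 baseline variables to compare (age, gender, HSI, weight, height, BMI, carbon monoxide, nicotine dependence, Q-Risk, SF-IPAQ, EQ5D-L). It does not define what counts as a difference. Assuming a 5% test on each, the chance of at least one is 1 − 0.95^11 = 43% if all are independent, and 1 − 0.95^6 = 26% if overlap leaves about six effective tests. On these assumptions the regression would be used fairly often.

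**5. Cost in precision of separate coefficients.** With residual SD s and n per arm, the pooled contrast has variance s²(1/(2n) + 1/n) = 1.5s²/n, and a two-arm contrast has 2s²/n. The ratio of standard errors is √(2/1.5) = 1.15. At n = 66 and s = 3.23 (unadjusted) these are 0.49 and 0.56 points. Power for a two-arm difference of 1.89 at two-sided 0.05 is 91.6% with 66 evaluable per arm. With 86 recruited it is 90.7% with 64 evaluable (25% dropout) and 88.9% with 60 (30% dropout). The planned size can therefore carry separate contrasts of that magnitude.

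The stated 66 is not what the stated inputs give: 2·(1.960 + 0.842)²·3.23²/1.89² = 45.9, so 46 per group (47 by the t-test). That is a separate matter and lends no support to this point.

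**6. Error rate, for the optional addition only.** In 400,000 simulated trials with no true differences (66 per arm), at least one of three pairwise tests at 0.05 was significant in 12.1%. When pairwise results were read only after a significant overall ANOVA, the rate was 5.0%. It was also 5.0% for A-B when A = B and C differed by 1.89.

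**The case against.** The strongest reply is that the lead analysis already keeps the arms apart. The ANOVA compares three groups and the intervals are between the three groups, so A-B can be read from there, and the regression is only a conditional supplement. This stands, and it limits the point. A reader might infer that the trial cannot answer the nicotine versus nicotine-free question at all; the document does not support that.

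A second reply is that pooling is nowhere stated, and the sentence may be loose wording for one coefficient per e-cigarette arm. That is possible, and it would agree with the Design section. But one estimate with one interval is what the sentence specifies, and an analyst following it would fit one parameter.

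A reader might also infer that the error rate is uncontrolled at about 12%. That would require three ungoverned pairwise claims. The text speaks of one interval, names no pairs, and sets a threshold for tests ("tests will be two-tailed with statistical significance being set at" 0.05) without promising a trial-wide rate. How pairwise results follow from the ANOVA is detail that a protocol article commonly leaves to the analysis plan, so its absence is not an error here.

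Nor is the sample-size contrast a further inconsistency. On the pooled reading it is the same contrast as the regression's; on the other reading, a number per group fits separate comparisons with NRT.

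**Conclusion.** The point holds for the adjusted analysis. When baseline differences trigger the regression, the result it specifies pools A and B against C and yields no adjusted A-B difference, contrary to the design and to a stated objective. It affects the primary outcome and the 6-month secondary outcomes analysed in the same way. The unadjusted ANOVA and its intervals are not affected.

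The size depends on how far A and B differ, which the plan does not state. With equal arms, the single coefficient misses each arm's effect by half the true A-B difference: by 0.945 points each way if A-B is 1.89. If A and B have the same effect there is no bias. The conclusion rests on reading the singular parameter as written.

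**What to change.** Replace the single-parameter sentence. State that the regression enters group as a three-level factor (two indicators) together with the stratification covariates, and that A-C, B-C and A-B are each reported with a 95% CI from that one model, for the primary outcome and for the 6-month secondary outcomes.

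Optionally, add that pairwise differences are interpreted only after a significant 2-df group test. With three groups this holds the familywise error of the tests at about 5%; the individual intervals remain ordinary 95% intervals. This is a clarification, not the repair of a demonstrated error. Its price is some power: for A-C = 1.89 with 60 to 64 evaluable per arm, simulated power is 86 to 89% if B equals A or C, and 81 to 84% if B lies midway, against 89 to 91% without the rule.

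The main change costs analysis wording only. Recruitment, visits and data collection stay as they are. Each separate contrast is about 15% less precise than a pooled one, which the planned numbers can absorb for a difference of 1.89.

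### No visit-specific comparison is expressly assigned to the 3-day and 3-month vascular outcomes, and the summary measure stated for the repeated visits cannot isolate the acute effect

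*Protocol article*

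**What the plan says.** The specific objectives (Protocol article, end of Background) ask for the three groups to be compared at two horizons: "both acutely (e.g. within 3 days of “quit date”) and in the medium term (6 months following “quit date". Under Outcome measures, the primary outcome is macro-vascular function (%FMD) at 6 months, and the first secondary outcome is "Micro- and macro-vascular function at 3 days to define acute treatment effects and 3 months". Under Follow-up visits, the only content given for Visit 2 is the vascular assessment.

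The Data analysis section makes three statements that bear on these outcomes:

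- "An Analysis of Variance (ANOVA) will be used to compare mean macro- and micro-vascular function between groups", with confidence intervals, and with multiple regression if the groups differ at baseline. No visit is named.
- "Secondary outcomes at 6-months will be analysed similarly".
- "For repeated assessments at baseline, and at all follow-up sessions a summary measure", such as an AUC, "will be calculated for each participant".

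The same section says that SPSS will be used "to carry out missing values imputation and statistical analysis" and that the analysis is by intention to treat.

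**The concern.** The second statement extends the ANOVA and regression to secondary outcomes at one visit, 6 months. The third gives the series of visits a single number per participant. Read in order, the 3-day and 3-month vascular outcomes are most naturally left to that single number. Any one summary over baseline and all follow-ups merges the acute effect with the later ones, so it cannot answer an objective that asks for the acute effect on its own.

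At stake are a named objective and a visit scheduled for it. If the AUC is what gets tested, a real 3-day difference may be missed, or a null AUC may be reported when early and late effects point in opposite directions. If the wording is instead taken to leave the choice open, visit-specific tests or the summary could be chosen after the data are seen.

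**Working it through.** The plan gives no figure for this point, so there is none to reproduce. The check asks how much of a 3-day effect survives in an AUC.

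**Inputs from the Protocol article.** Visits at baseline, within 3 days of the quit date, 3 months and 6 months (Follow-up visits). Quit date usually within a week of baseline or, in Group C, of the first clinic appointment (Intervention). SD of %FMD 3.23, planning difference 1.89, 66 evaluable per group (Sample size). Two-sided 5% level (Data analysis).

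**Assumptions not in the document.** Trapezoidal rule in calendar time; visits at days 3, 90 and 180 after the quit date; baseline 0, 7 or 14 days before it; SD 3.23 at every visit; equal between-visit correlation ρ of 0.3 to 0.7.

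**Step 1: weights.** Each visit's weight is half the sum of its adjacent intervals, divided by the total span. With baseline 7 days before the quit date, the intervals are 10, 87 and 90 days (total 187):

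- baseline: 5/187 = 2.7%
- day 3: (5 + 43.5)/187 = 25.9%
- month 3: (43.5 + 45)/187 = 47.3%
- month 6: 45/187 = 24.1%

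| Baseline before quit date | Baseline | Day 3 | Month 3 | Month 6 |
|---|---|---|---|---|
| 0 days | 0.8% | 25.0% | 49.2% | 25.0% |
| 7 days | 2.7% | 25.9% | 47.3% | 24.1% |
| 14 days | 4.4% | 26.8% | 45.6% | 23.2% |

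Day 3 weighs as much as month 6 only because the next visit is 87 days later.

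**Step 2: what happens to an effect of 1.89** (7-day gap, AUC divided by its span so that it is in %FMD units):

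- Day 3 only: 1.89 × 0.259 = 0.49, a dilution of 1/0.259 = 3.9-fold.
- −1.89 at day 3, 0 at month 3, +1.89 at month 6: 1.89 × (45 − 48.5)/187 = −0.04, so the two effects cancel almost completely.
- 1.89 at all three follow-ups: 1.89 × 0.973 = 1.84, so a sustained effect is kept.

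**Step 3: power for a day-3-only effect.** The SD of the averaged AUC is 3.23 × √(ρ + (1 − ρ)Σw²), with Σw² = 0.350. This gives 2.38, 2.65 and 2.90 for ρ = 0.3, 0.5 and 0.7. Power is Φ(Δ/(SD × √(2/66)) − 1.96).

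- AUC, ρ = 0.5: 0.49/(2.65 × 0.174) − 1.96 = −0.90, so power is 18%. Over ρ = 0.3 to 0.7 it runs from 22% down to 16%.
- The same difference tested at day 3 alone: 1.89/(3.23 × 0.174) − 1.96 = 1.40, so power is 92%.

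The 92% exceeds the article's 80% because its stated inputs give 46 per group by the usual two-group formula, not 66. That is a separate matter; 66 is used here only as the planned number.

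**The case against.** The strongest reply is that the text is ambiguous rather than wrong. The ANOVA sentence names no visit, and its wording matches the secondary outcome that covers 3 days and 3 months, so it can be read to include them. The AUC is only an example, and nothing says that it replaces comparisons at each visit. The trapezoid and the calendar-time weights are assumptions, and a statistical analysis plan that is not shown may define the summary. The pattern of opposite effects is constructed, since the article gives no expected course over time. All of this stands, and it limits the point to an unassigned comparison. It does not remove it: the method is expressly extended only to 6 months, and any single summary over all visits, AUC or other, merges the time points. The mismatch lies between a stated method and a stated objective.

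Some stronger readings are tempting but not supported:

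- *The 6-month effect is lost in the AUC.* It is not. Six-month FMD is the primary outcome, and micro-vascular function at 6 months is a separate secondary outcome. Both fall under the ANOVA and regression.
- *The AUC strictly needs every visit.* Imputation is planned, although its method is not given, and a trapezoid can bridge a missed intermediate visit at the price of an interpolation assumption.
- *The AUC limits the data to about 60–64 of 86 per group.* That figure is 86 × 0.70 to 86 × 0.75, the planned 25–30% dropout, which affects any 6-month analysis equally.
- *Including baseline distorts the AUC badly.* Its weight is only about 1–4%.

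**Conclusion.** The point holds as a gap in assignment. The Data analysis section gives the 3-day and 3-month vascular outcomes, and with them the acute objective, no express visit-specific comparison, and the one method it states for the repeated visits cannot supply it.

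If a trapezoidal AUC were the test, a 3-day-only difference would shrink about four-fold, and power at 66 per group would fall from 92% to about 16–22%. The weights rest on the assumed rule and visit days, and change little over a baseline gap of 0 to 14 days. The power figures also rest on an equal SD at every visit and correlations of 0.3 to 0.7. If the ANOVA was always meant to be run at each visit, none of this loss occurs and only the wording needs repair. The primary analysis is untouched. Correction is still worthwhile, because the acute effect is a named objective and the data for it will be collected anyway.

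**What to change.** State in Data analysis that micro- and macro-vascular function will be compared between groups at 3 days, 3 months and 6 months, adjusted for the baseline value of the same measure and for the stratification factors (gender and packet-years). Two suitable ways are:

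- a mixed model for repeated measures on Visits 2 to 4 with group, visit, group × visit and baseline × visit terms, reporting the group differences with 95% CIs at each visit; this also keeps participants who have only some of the visits;
- ANCOVA at each visit.

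Keep the AUC, labelled as a supplementary summary of the whole course, and state how it is calculated.

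The cost is a change of wording, slightly more analysis, and more secondary comparisons to report. No new visits, measurements or participants are needed, and the planned software can fit either model.
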